### Follow-up

Outcomes are assessed pre-operatively, after 6 weeks, and after 3 and 6 months, being the moments of routine control assessments and be registered on a case record form (CRF) by the treating physician and checked by the research nurse (status review) (see figure 1). Costs are assessed by a cost assessment (CRF and patient questionnaire). The doctor registers costs on a CRF related to the use of operation materials (disposables), operating time, duration of hospital stay, and treatment of complications.

All adverse events are followed until they have abated, or until a stable situation has been reached.

Data regarding quality of life (SF-36, EQ-5D), pain (VAS), Body Image Scale (BIS), sexuality (SAQ) and additional homecare are assessed with help of self reported questionnaires 6 weeks, 3 and 6 months after the operation (see figure 1).

### Monitoring

#### Pre start monitoring

To minimize complications due to inexperience, all inexperienced general gynecologists are trained by a visiting gynecologist with experience in laparoscopy until sufficient laparoscopic skills are reached, before study entry. Only gynecologists who reached sufficient scores (≥ 28 points) on OSATS in performing two independent TLH procedures are allowed to participate in the study. The study coordinator facilitates centers in order to get approval of the medical ethical committee. As the study is set in a national research consortium, allied research nurses are responsible for collecting data, monitoring of the study and promote the study at the local centers.

A kick off meeting is held by the study coordinator in every participating center. During this meeting the content and inclusion procedure of the study is explained.

#### On site monitoring

During the study period, frequent contact and assistance of the coordination center is enabled by regular telephone calls and visits to all local centers. Furthermore, every three months newsletters by email are send to the centers in order to inform the gynecologists about study progress and bring new items under their attention.

Publicity of the study is realized by means of presentations held on national and international congresses. Thereby, the study protocol and other related study documents are available online. *http://www.studies-obsgyn.nl/home/page.asp?page_id=418*.

Case record forms, checked by the research nurse of concerned center and self reported patient questionnaires are send to the Trial Coordination Center (TCC) of the coordinating center. The TCC takes care of entry and validating data of case record forms and importing patient questionnaires. In case of discrepancies or inaccuracies found in the case record forms, queries are send to the centers in question. Final monitoring will be done by the study coordinator by visiting randomly selected centers and checking a part of the case record forms once again.

### Study parameters/endpoints

#### Main study parameter/endpoint

Our primary endpoint is: major complication rate. The following major complications are registered: injuries of bowel, bladder, ureter, vessel, nerves; thrombo-embolic events such as DVT (Deep Venous Thrombosis) or pulmonary embolism; haematoma requiring surgical intervention; hemorrhage requiring transfusion and/or surgical intervention; wound dehiscence requiring surgical intervention or re-admission; wound infections including vaginal vault abscess, requiring surgical intervention and/or prolonged hospital stay and/or readmission and/or treatment; other major complications.

The severity of a complication is scored according to the Common Terminology Criteria CTCAE version 3.0. An independent Complication Review Board of three experienced clinicians is asked to assess and judge all recorded complications and differentiate between major and minor complications, blinded to treatment arm. This Complication Review Board decides also if the complication is related to the operative procedure, as expressed by the following statements: not related, unlikely related, possibly related, probably related or definitely related. *http://ctep.cancer.gov/protocolDevelopment/electronic_applications/docs/newadverse_2006.pdf*

#### Secondary study parameters/endpoints

1) Cost effectiveness

2) Minor complications. Outcomes are assessed by analyzing the CRF. An independent clinical review panel differentiates between major and minor complications, blinded for treatment arm and also assess whether the complication is related to the operative procedure.

3) Quality of life (SF-36 and EUROQOL), sexual functioning (Sexual Activity Questionnaire), Body Image Scale (BIS) and pain (Visual Analogue Scale).

### Premature termination of the study

The study will be terminated prematurely if the disadvantages of participation may be significantly greater than was foreseen in the research proposal. All complications are assessed and recorded by an independent clinical review panel. This panel assesses if the complications occurring in the TLH group do exceed in amount or severity the complications occurring in the standard of care (TAH) group. If so, the study will be terminated.

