### Randomization and collection of baseline data

The patients to be enrolled in this trial are allocated to the TAH or TLH arm by computer randomization. For randomization, blocks of x patients are created such that balance is enforced within each block, stratified per center. Randomization is 2:1 for intervention to provide more exposure to data on the new laparoscopic procedure. We also expect a better enrolment in the study if the patients have a twofold chance of being allocated to the laparoscopic group as the reduced morbidity seems to be substantial. At study entry, all woman have baseline demographic, past gynecologic and medical history recorded in a case record form (CRF). After randomization, but prior to surgical treatment, patients are asked to fill in a questionnaire, consisting items regarding: quality of life (SF-36, EQ-5D), pain (VAS), Body Image Scale (BIS), sexuality (SAQ) and a questionnaire on additional homecare. (see figure 1)

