### Statistical analysis

#### Sample size

Sample size estimates are based on the ability of the study to detect changes in the primary outcome measure, rate of major complications. In this study, we choose for an unbalanced randomization (2(TLH+BSO):1(TAH+BSO)). Group sample sizes of 161 and 81 achieve 80% power to detect a difference of 0.15 between the null hypothesis that the major complication rate is 25% in both the TAH + BSO and the TLH + BSO group and the alternative hypothesis that we will observe a complication rate of 25% in the TAH + BSO group and of 10% in the TLH + BSO group, using a two-sided Chi-square test with continuity correction and with a significance level of 0.05. Assuming a drop-out percentage of 10%, 275 patients are needed.

The assumptions regarding these expected complication rates are based on the complication rates reported in (retrospective) studies comparing TAH with TLH. In addition, this is supported by the major complication rate of 9.26% that we found during the learning curve in our pilot study. The drop-out percentage of 10% can be expected when patients, after randomization, are unhappy with their allocated treatment and choose to end their participation in the study or due to incomplete or lost data.

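### The mandatory stopping rule compares the amount of complications between arms randomised 2:1 without a denominator or margin, and assigns the comparison to a panel described as blinded to arm

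*Protocol article*

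**What the plan says.** The protocol article, under Premature termination of the study, opens with a general condition: "The study will be terminated prematurely if the disadvantages of participation may be significantly greater than was foreseen in the research proposal". It then says who does the work: "All complications are assessed and recorded by an independent clinical review panel". That panel is to judge whether "complications occurring in the TLH group do exceed in amount or severity the complications occurring in the standard of care (TAH) group". The consequence is mandatory: "If so, the study will be terminated".

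Two other parts of the article bear on this rule.

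- **Allocation.** Under Randomization and collection of baseline data: "Randomization is 2:1 for intervention to provide more exposure to data on the new laparoscopic procedure". The Sample size section repeats the 2:1 ratio and gives 161 TLH and 81 TAH patients.
- **Blinding.** Under Secondary study parameters/endpoints: "An independent clinical review panel differentiates between major and minor complications, blinded for treatment arm". Under Main study parameter/endpoint, a Complication Review Board of three clinicians is to "differentiate between major and minor complications, blinded to treatment arm".

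**The concern.** There are two difficulties, and both lie in what the article states.

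First, an amount has no denominator. With twice as many TLH patients, equal risk produces about twice as many TLH complications whatever the true rate. A rule that stops on any TLH excess in amount would then fire because of the allocation ratio and not because of harm. Any excess also leaves no room for chance.

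Second, a panel that does not know the arm cannot compare the arms. If it is unblinded in order to do so, and goes on adjudicating, the stated protection of the primary endpoint is weakened. That protection matters here, because the surgeon and patient know the operation, the split between major and minor is a matter of judgement, and the list of major complications ends with an open category.

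A trial in which TLH is as safe as TAH, or moderately safer, could be ended by its own rule. Alternatively, the rule could be ignored as unworkable, leaving no usable safety criterion.

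**Working it through.** **Inputs.** From the Sample size section: 161 TLH and 81 TAH patients; 25% in both arms under the null; 25% TAH and 10% TLH under the alternative; two-sided chi-square test with continuity correction at 0.05; 10% drop-out; 275 in total.

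**Assumptions.** The rule covers all complications, but the article gives no rate for minor ones, so the major-complication rates are used. Each patient counts at most once. The timing of looks is not stated, so any timing below is assumed.

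**The plan's own figure.** The continuity-corrected formula at 25% versus 10% with ratio 2 gives 81 TAH and 162 TLH, against the stated 81 and 161. Exact power at 81/161 is 80.7%. Allowing for drop-out, 242 / 0.9 = 269, slightly below the stated 275. The sample size is not in question.

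**Step 1: amount read as a count.** Let X ~ Bin(161, p_TLH) and Y ~ Bin(81, p_TAH), independent. The rule fires if X > Y, with probability

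P(X > Y) = Σ_y P(Y = y) · P(X > y).

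Expected counts are 161 · p_TLH and 81 · p_TAH. They are about equal when p_TLH is 81/161 ≈ 0.50 of p_TAH.

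**Step 2: amount read as a rate.** The rule fires if X/161 > Y/81, summed over the same joint distribution.

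One look at 161/81:

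| TLH v TAH rate | Expected events | Count reading | Rate reading |
|---|---|---|---|
| 25% v 25% | 40.3 v 20.3 | 99.8% | 51% |
| 20% v 25% | 32.2 v 20.3 | 96.4% | 20% |
| 15% v 25% | 24.2 v 20.3 | 71.4% | 4% |
| 12.5% v 25% | 20.1 v 20.3 | 45.5% | 1.1% |
| 10% v 25% (planned) | 16.1 v 20.3 | 19.6% | 0.2% |

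Hand check of the last count figure by normal approximation: the mean of X − Y is 16.1 − 20.25 = −4.15. The variance is 161 · 0.10 · 0.90 + 81 · 0.25 · 0.75 = 14.49 + 15.19 = 29.68. So P(X − Y ≥ 0.5) = P(Z > 4.65 / 5.45) = P(Z > 0.85) ≈ 0.20, which agrees.

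**Step 3: half-way.** Half of 275 is about 138, or 92 TLH and 46 TAH.

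- Count reading: 98.6% at equal 25% rates and 24.6% at the planned effect.
- Rate reading: 48% and 1.2%.

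**Step 4: repeated looks.** With three looks assumed at 25%, 50% and 75% of recruitment, simulation gives these probabilities of firing at least once.

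- Count reading: above 99% at equal 25% rates and about 41% at the planned effect.
- Rate reading: about 66% and 6%.

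**Step 5: who applies the rule.** No arithmetic applies; the sections are set side by side.

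| Section | Body | Task | Knows the arm? |
|---|---|---|---|
| Main study parameter/endpoint | Complication Review Board | Major v minor, relatedness | No |
| Secondary study parameters/endpoints | Independent clinical review panel | Major v minor, relatedness | No |
| Premature termination of the study | Independent clinical review panel | TLH v TAH comparison | Must see results by arm |

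The last two rows use the same name. The first two share task and blinding, so they are apparently the same body. The article describes no separate unblinded committee and no release of by-arm data.

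**The case against.** **Amount may mean rate.** The article does not say count. It defines the primary endpoint as a rate and summarises discrete variables by frequencies or proportions, so a panel in a declared 2:1 trial might well allow for arm size. This stands as a fair reading: it removes the artefact and leaves little risk at the planned effect. It does not rescue the rule, because a bare excess still stops an equal-arms trial about half the time at one look. The wording also does not settle the matter, although the article uses rate elsewhere when it means one.

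**The opening sentence is a qualifier.** It asks for disadvantages significantly greater than foreseen. That is true, but it is unquantified and compares experience with the proposal, not TLH with TAH. The operative comparison has no such qualifier, and its consequence is mandatory.

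**Looks and boundaries belong in the full protocol.** This largely stands. The absence of a schedule is not the point here. The point is a stated criterion that fits badly with the stated allocation, and a stated task that fits badly with the stated blinding.

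**Blinding can coexist with monitoring.** It can. The blinding attaches to classification, and a panel could classify blind and later see a by-arm summary of closed cases. That the panel and the board are one body is also an inference from name and task. The article does not describe such a sequence, so the sections need reconciling, but a breach of blinding is not established.

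**A stronger reading is tempting.** A reader might infer that the rule tends to stop the trial whenever TLH is equal or better. The figures do not support that. Even as a count, the rule fires less often than not at one look once the TLH rate falls to about half the TAH rate, and at the planned effect the chance is about 20%.

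**Conclusion.** The concern holds in this form: a mandatory rule with no denominator under 2:1 allocation, no margin, and an assessor described as blinded. On the count reading it would almost certainly stop a trial of equal arms (99.8% at 161/81) and would probably stop one in which TLH is moderately better (96% at 20% versus 25%, 71% at 15% versus 25%). At the planned effect, stopping is a material risk and not the expected result: 20% at one look, and about 41% over three assumed looks. On the rate reading the planned-effect risk is 0.2% at 161/81 and 1.2% at 92/46, but equal arms still trigger stopping about half the time at one look.

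These sizes rest on major-complication rates standing in for all complications; the multi-look figures also rest on assumed timing. The doubling of expected counts at equal risk depends on neither. The severity limb cannot be quantified from the article. The conflict over blinding is firm as a need to reconcile the sections, and less firm as to whether panel and board are one body.

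**What to change.** Under Premature termination of the study:

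1. Replace amount by the proportion of randomised patients in each arm with at least one adjudicated complication.
2. Make the trigger an excess in that proportion beyond a pre-stated statistical margin or boundary, at pre-stated looks, in place of any excess.
3. Keep the severity limb, also as a per-arm proportion, for example by CTCAE grade, with its own pre-stated margin.
4. State that adjudication stays blinded. The Trial Coordination Center releases the by-arm table only for events whose adjudication is locked, and only to people who do not adjudicate further events.
5. Use one name for the adjudicating body in all three sections, or say that there are two bodies and what each may see.

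The cost is a paragraph of protocol text and a short by-arm table from the existing coordination centre, with no extra patients or visits. The downside is small but real: looks must be scheduled, a boundary chosen, and a non-adjudicating recipient named, which the article does not at present provide for.

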### Statistical analysis

#### Sample size

Sample size estimates are based on the ability of the study to detect changes in the primary outcome measure, rate of major complications. In this study, we choose for an unbalanced randomization (2(TLH+BSO):1(TAH+BSO)). Group sample sizes of 161 and 81 achieve 80% power to detect a difference of 0.15 between the null hypothesis that the major complication rate is 25% in both the TAH + BSO and the TLH + BSO group and the alternative hypothesis that we will observe a complication rate of 25% in the TAH + BSO group and of 10% in the TLH + BSO group, using a two-sided Chi-square test with continuity correction and with a significance level of 0.05. Assuming a drop-out percentage of 10%, 275 patients are needed.

The assumptions regarding these expected complication rates are based on the complication rates reported in (retrospective) studies comparing TAH with TLH. In addition, this is supported by the major complication rate of 9.26% that we found during the learning curve in our pilot study. The drop-out percentage of 10% can be expected when patients, after randomization, are unhappy with their allocated treatment and choose to end their participation in the study or due to incomplete or lost data.

#### Descriptive statistics

Primary endpoints will be analyzed according to the intention-to-treat principle.

Descriptive statistics for QOL (SF-36, EQ-5D, VAS, BIS, SAQ) and a questionnaire on additional homecare) will be calculated for each randomization group at each assessment. Similarly, descriptive statistics will also be calculated for other outcomes, such as pain scores, and analgesic consumption, etc. Continuous variables will be assessed for normality and equality of variances between groups. Discrete variables (e.g. presence/absence of post-operative infection) will be summarized by frequencies/proportions. For continuous variables, analysis of variance and/or regression will be used, where appropriate. If assumptions for these tests are violated, alternative non-parametric tests will be used. Difference between groups with respect to discrete variables will be evaluated by using chi-squared tests.

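### An assumption check on the trial's own data decides whether quality-of-life and other continuous secondary outcomes get a linear model or an unnamed non-parametric test

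*Protocol article*

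**What the plan says.** The rule is in the protocol article, Statistical analysis, under Descriptive statistics. Three consecutive steps matter:

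- the check: "Continuous variables will be assessed for normality and equality of variances between groups";
- the default: "For continuous variables, analysis of variance and/or regression will be used, where appropriate";
- the switch: "If assumptions for these tests are violated, alternative non-parametric tests will be used".

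The section does not say what counts as a violation, which non-parametric test replaces the default, or which covariates enter the regression. An earlier sentence in the section says that summaries of the quality-of-life instruments "will be calculated for each randomization group at each assessment". That sentence concerns description, not testing.

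The same instruments are collected before and after surgery. Randomization and collection of baseline data has: "After randomization, but prior to surgical treatment, patients are asked to fill in a questionnaire". Follow-up has: "self reported questionnaires 6 weeks, 3 and 6 months after the operation". Quality of life, sexual functioning, body image and pain are secondary endpoints, and quality of life is part of the stated aim. The primary endpoint, the major complication rate, is binary and does not come under this rule.

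**The concern.** The article fixes a rule here, so this is not a detail left to a fuller document. Under that rule the observed distribution selects the method, and with it the quantity reported. Analysis of variance or regression estimates a difference in means. A standard two-sample rank test, the usual non-parametric replacement, tests a shift in ranks. It gives no mean difference and ordinarily takes no covariate. One instrument could end as a mean difference with an interval and another as a p-value, for reasons unknown until the data are seen.

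Two things are at stake. The first is an interpretable effect size for each instrument, stated in advance. The second is precision: a score taken before surgery usually predicts the same score afterwards, and an outcome moved to a rank test would normally lose that information.

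**Working it through.** **Group sizes.** The Sample size section gives 161 TLH and 81 TAH patients (25% v 10%, two-sided 0.05, continuity-corrected chi-square, 80% power), and 275 in total after 10% drop-out. Check of the plan's figure:

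- pooled rate = (81 × 0.25 + 161 × 0.10)/242 = 0.1502
- null SE = √[0.1502 × 0.8498 × (1/81 + 1/161)] = 0.0487
- alternative SE = √[0.25 × 0.75/81 + 0.10 × 0.90/161] = 0.0536
- continuity term = 0.5 × (1/81 + 1/161) = 0.0093
- z = (0.15 − 0.0093 − 1.96 × 0.0487)/0.0536 ≈ 0.846, power 80.1%
- drop-out: 242/0.9 = 268.9, so 269 against the stated 275

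The sizes hold, and this point does not affect them. No power figure is given for quality of life. At 2:1, 275 patients are about 183 v 92.

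**How often the switch fires, and its effect on type I error.** Simulation under no treatment effect, 81 v 161, 6,000 runs per shape. If Shapiro-Wilk gave p < 0.05 in either arm, Mann-Whitney was used; otherwise the t-test. The shapes and the pre-test are assumptions, because the article names neither. The equal-variance check was not simulated. Simulation standard error near 0.05 is √(0.05 × 0.95/6000) = 0.003.

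| Assumed shape | Switched | Error, rule followed | Error, smaller p-value taken |
|---|---|---|---|
| Normal | 10% | 0.053 | 0.063 |
| Lognormal | 100% | 0.049 | 0.076 |
| Bounded, skewed 0–100 score | 100% | 0.047 | 0.058 |
| Exponential | 100% | 0.055 | 0.078 |

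Followed mechanically, the rule keeps its error rate. Only choosing the smaller of the two p-values raises it, and the article does not permit that.

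**Precision from the pre-operative score.** At one visit, baseline adjustment multiplies the variance by 1 − ρ², where ρ is the correlation between baseline and follow-up. The documents give no ρ, so a range is shown. The difference detectable with 80% power, in SD units, is d = (1.960 + 0.842) × √(1/n + 1/(2n)) × √(1 − ρ²), with n = N/3 in the TAH arm.

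| ρ (assumed) | Variance factor | d at N = 275 | d at N = 242 |
|---|---|---|---|
| no adjustment | 1 | 0.358 | 0.382 |
| 0.3 | 0.91 | 0.342 | 0.364 |
| 0.5 | 0.75 | 0.310 | 0.331 |
| 0.6 | 0.64 | 0.287 | 0.306 |

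In equivalent sample size, 1/0.91 = 1.10, 1/0.75 = 1.33 and 1/0.64 = 1.56.

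**The rule against the proposed model.** With 161 v 81 patients, an assumed bounded skewed score and a latent shift of 0.38 SD, the switch fired in about 100% of runs and the two-stage rule had about 76% power. A baseline-adjusted linear model with robust standard errors had about 79%, 85% and 91% at ρ of 0.3, 0.5 and 0.6. A repeat of this simulation agreed closely. In it an unadjusted t-test did about as well as the rank test, so the gain comes from the baseline score and not from avoiding ranks as such.

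**The case against.** The best defence is that the rule does little harm. Its type I error stays near nominal, rank tests are valid and often efficient for skewed scores, and preferring mean differences is partly a matter of taste. This largely stands: the point is not about false positives, nor is a rank test a poor test. What remains is that the reported effect measure depends on the data, and that the usual replacement has no place for the baseline.

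A second defence is that regression is allowed, its covariates are not listed, and a condensed article may leave them to the full protocol. This also stands. A reader might infer that the plan never uses the baseline. The article does not say so, and the variance figures apply only where baseline is in fact left out. The narrower point holds: once an outcome is switched to an ordinary rank test, baseline normally drops out, whatever the regression would have contained.

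A reader might also infer that the arms are tested separately at each visit, that patients who miss a visit are lost from that comparison, and that dozens of tests result. The wording about each assessment governs descriptive summaries, repeated-measures forms are not excluded, no missing-data rule is stated, and the number of scores is not given. None of these readings is supported.

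**Conclusion.** The point holds for continuous secondary outcomes only. The article commits to a data-driven choice between a linear analysis and an unnamed alternative, with no criterion. For skewed, bounded scores the alternative would become the usual analysis, with no mean difference and normally no baseline adjustment. The cost is a data-dependent effect measure, plus a variance reduction forgone of 9% to 36% for ρ between 0.3 and 0.6 if baseline is otherwise left out. In the simulated example this was about 3 to 15 percentage points of power (79 − 76 to 91 − 76). These sizes rest on assumed correlations, an assumed score shape and Shapiro-Wilk as the pre-test. The primary endpoint, its sample size and its test are unaffected. The change is worth making because quality of life is a named aim, but the trial's main conclusion does not depend on it.

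**What to change.** Delete the switching sentence. Pre-specify one linear mixed model per instrument with arm, visit, arm-by-visit interaction, the pre-operative score already collected, and centre (the stratification factor). Report mean differences with 95% confidence intervals from robust or bootstrap standard errors. With about 183 v 92 patients this is adequate for means of skewed scores. Keep rank tests, if wanted, as a named sensitivity analysis.

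The pre-operative questionnaire is completed after randomisation, so it may already reflect knowledge of the allocation. Report the estimate without that covariate as a further sensitivity analysis.

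The cost is a change of analysis wording and modest programming. No new data are needed, because the model uses the existing pre-operative score. The model still gives a contrast at each visit, so it does not reduce the number of comparisons.

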**Methods:**

A multi centre randomized clinical phase 3 trial, including 5 university hospitals and 15 regional hospitals in the Netherlands. Only gynecologists trained in performing a TLH are allowed to participate. Inclusion criteria: Patients with a clinical stage I endometrioid adenocarcinoma or complex atypical hyperplasia are randomized in a 2:1 allocation to receive TLH or TAH. The main outcome measure is the rate of major complications, as assessed by an independent clinical review board. In total, 275 patients are required to have 80% power at α-0.05 to detect a significant difference of 15% complication rate. Secondary outcome measures are 1) costs and cost-effectiveness, 2) minor complications, and 3) quality of life. All data from this multi center study are reported using case record forms. Data regarding quality of life, pain, body Image, sexuality and additional homecare are assessed with self reported questionnaires.

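### The primary chi-square ignores the centre strata used in randomisation, and the article leaves open whether a continuity correction, worth about 5 points of power, applies in the analysis

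*Protocol article*

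**What the plan says.** Four statements in the protocol article bear on this.

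- **Randomization and collection of baseline data:** within a 2:1 allocation, "balance is enforced within each block, stratified per center".
- **Abstract, Methods:** the trial runs in 20 hospitals, "including 5 university hospitals and 15 regional hospitals in the Netherlands". Aims&design says at least 15 centres.
- **Sample size:** "Group sample sizes of 161 and 81 achieve 80% power to detect a difference of 0.15", "using a two-sided Chi-square test with continuity correction and with a significance level of 0.05". The alternative is that "we will observe a complication rate of 25% in the TAH + BSO group and of 10% in the TLH + BSO group". The section adds: "Assuming a drop-out percentage of 10%, 275 patients are needed".
- **Descriptive statistics:** the primary endpoint is analysed by intention to treat. For categorical outcomes in general, "Difference between groups with respect to discrete variables will be evaluated by using chi-squared tests".

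The article names a test in two places. Neither includes centre, and only the sizing statement mentions a continuity correction.

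**The concern.** There are two separate issues.

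**Centre.** When allocation is balanced within centres and centre predicts outcome, a test that ignores centre uses a variance that is too large, so its true type I error falls below the nominal level. Centre could plausibly predict outcome here. The Background says complications are more frequent during the learning curve, and the Discussion says most procedures are done in general hospitals by general gynecologists.

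**Continuity correction.** The corrected and uncorrected chi-square are different tests. The corrected one runs well below 5% in a trial of this size. Leaving the choice open means a borderline result could be significant under one reading and not under the other.

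At stake are some avoidable conservatism and an ambiguity in the primary test. A false positive finding is not the worry, because both effects work against rejection.

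**Working it through.** **Inputs from the article:** 25% (TAH) and 10% (TLH), two-sided 0.05, 80% power, 2:1 allocation, 81 and 161 patients, 20 centres (or at least 15). **Assumed:** centre sizes, and the between-centre SD on the logit scale.

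**1. Reproduce the stated sample size.** With p̄ = (0.25 + 2×0.10)/3 = 0.15, the uncorrected TAH group size is

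n = [1.96·√(1.5×0.15×0.85) + 0.8416·√(0.25×0.75 + 0.10×0.90/2)]² / 0.15² = (0.857 + 0.406)²/0.0225 = 70.9, so 71 (with 142 TLH).

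With the correction, n_c = (n/4)·[1 + √(1 + 2×3/(n×2×0.15))]² = 17.72 × (1 + 1.1323)² = 80.6, so 81, with 2 × 80.6 ≈ 161 TLH. The stated 161 and 81 are therefore the continuity-corrected figures. Drop-out: 242/0.9 = 269, and the stated 275 covers it.

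**2. Approximate power at 81/161.** The pooled rate is (20.25 + 16.1)/242 = 0.1502. The null SE is √(0.1502×0.8498×(1/81 + 1/161)) = 0.0487, and the alternative SE is √(0.1875/81 + 0.09/161) = 0.0536. The correction is ½(1/81 + 1/161) = 0.0093.

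- Corrected: Φ[(0.15 − 0.0093 − 1.96×0.0487)/0.0536] = Φ(0.85) = 80.1%.
- Uncorrected: Φ[(0.15 − 1.96×0.0487)/0.0536] = Φ(1.02) = 84.6%.

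**3. Exact enumeration at 81/161, no centre effect.** This sums the binomial probabilities of all tables that the test rejects.

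| Test | Power | Type I error at common rate 10% / 15% / 25% |
|---|---|---|
| Chi-square, corrected | 80.7% | 2.8% / 3.0% / 3.4% |
| Chi-square, uncorrected | 86.0% | 4.9% / 5.1% / 4.95% |

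The correction alone costs 86.0 − 80.7 = 5.3 points.

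**4. Effect of stratifying.** There were 40,000 simulated trials per setting, with 81/161 patients in 15 or 20 centres of equal or skewed size and allocation near 2:1 in each. Centre effects were normal on the logit scale, with the overall rates held at 25% and 10% (power) or 25% in both arms (type I error). Ranges cover the four centre layouts. Simulation standard error is about 0.2 points for power and 0.1 for type I error. Both tests are uncorrected.

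| Assumed centre SD | Chi-square: power; type I | CMH: power; type I | Power change from stratifying |
|---|---|---|---|
| 0 | 85.8–86.3%; 4.8–5.1% | 85.1–85.6%; 4.8–5.0% | −0.8 to −0.6 |
| 0.5 | 85.9–86.2%; 4.4–4.6% | 85.9–86.3%; 4.8–5.0% | −0.1 to +0.1 |
| 1.0 | 86.7–87.2%; 3.5–3.8% | 88.2–88.8%; 5.1–5.2% | +1.5 to +1.7 |
| 1.5 | 87.0–88.5%; 2.5–2.8% | 90.7–91.9%; 4.9–5.1% | +3.4 to +3.7 |

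Allowing one simulation standard error, the chi-square type I error at SD 1.0 is 3.4–3.9%. Compare within rows only: holding the overall rates fixed makes the within-centre effect larger as the SD rises.

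With the correction in both tests, stratifying gains 0–0.2 points at SD 0, 0.6–0.8 at SD 0.5, 2.2–2.5 at SD 1.0 and 4.6–4.8 at SD 1.5. The corrected CMH stays at 3.2–3.4% type I error throughout, so stratifying without dropping the correction does not restore the nominal level.

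**5. Changing both at once.** Uncorrected CMH exceeds the corrected chi-square by 4.5–4.7 points at SD 0, 5.2–5.4 at SD 0.5 and 6.4–6.8 at SD 1.0. At SD 0, removing the correction accounts for all of this.

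**The case against.** The strongest objection is that this is detail an article may leave to the full protocol or SAP. The chi-squared sentence sits under Descriptive statistics and covers discrete variables in general, and silence about strata does not exclude them. It is also fair that the analysis text never commits to the correction, that no planned power is lost, and that the article reports no between-centre variation. Pre start monitoring requires an OSATS score of at least 28 in two independent procedures, which should narrow differences in skill. Strata would also be sparse: about 36 expected events (20.25 + 16.1) over 20 centres is under two per centre.

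Much of this stands, and it limits the point to a modest one. It does not remove it. The article does name its test, twice, without centre, and the two descriptions leave the correction unsettled. CMH pools information over sparse strata, and the simulated cost of that sparseness is under one point.

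Three stronger readings are tempting and are not supported:

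- **Ignoring centre costs 5 points of power.** Like for like, stratifying is worth roughly nothing up to SD 0.5. Even SD 1.5 gives only 3.4–3.7 points between uncorrected tests and 4.6–4.8 between corrected ones, and nothing in the article supports so large an SD.
- **The primary test runs at 2–3%.** That needs the correction to be used. Without it and without centre differences, type I error is 4.9–5.1%.
- **The trial is underpowered or wrongly sized.** The stated figures reproduce for the test they name.

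**Conclusion.** The point holds in a limited form. The named tests do not follow the centre-stratified randomisation, and the article does not settle whether the primary test carries a continuity correction.

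The correction is the larger matter: if used, it gives up about 5 points of power (80.7% against 86.0%) and runs the test at 2.8–3.4%. This result is exact and depends only on the stated group sizes and the event rates shown.

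Ignoring centre is the smaller matter. It makes even the uncorrected test mildly conservative if centres differ, and stratifying mainly restores the nominal error rate. The size of this effect rests wholly on assumed between-centre SDs and centre sizes.

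Any departure is conservative, so a positive result would not be undermined. The change is worth making because it costs little.

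**What to change.** State one primary test: a Cochran-Mantel-Haenszel test of major complications by allocated arm, stratified by centre, two-sided at 0.05, without continuity correction. Report a centre-stratified risk difference with its 95% CI. Fix a rule for merging small centres before the allocation is revealed to the analyst, since a centre with no events or with only one arm contributes nothing to the test. Keep the unstratified chi-square as a sensitivity analysis, and say there whether it is corrected.

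The cost is a few sentences in the analysis section and no extra patients. If centres do not differ, stratifying costs up to about 0.9 points of power (86.0% exact for the uncorrected chi-square against 85.1% for the lowest simulated CMH value), and power still stays above the planned 80%. The sample size of 275 need not change.
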